#### Postural Sway: Center of Pressure

COP displacement times series obtained from the force platform will be down sampled to 100 Hz and subsequently will be processed using a low-pass filter at 5 Hz (fourth-order, zero-phase-lag, Butterworth) [45]. The mean velocity, root mean square, and maximum range of the COP displacement will be computed to evaluate postural sway [46].

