#### AMTI Force Plates

Postural control as the COP movement will be measured with an AMTI force platform (Advanced Mechanical Technology Inc.). The force platform measures the 3 force components, *F_x_*, *F_y_*, and *F_z_* (where *x*, *y*, and *z* are the medial–lateral, anterior–posterior, and vertical directions, respectively), at the sampling frequency of 1200 Hz. The AMTI force plate is a static-force measurement system and is a computer-based system which synchronizes with a computer using a serial link. The COP movement track data (in millimeter) will be collected for each participant and will be converted into mediolateral and anterior–posterior components for analysis.

Participants will stand on the force plate with arms relaxed at their sides. Participants will be asked to stand with their feet shoulder width apart. They will be instructed to maintain their gaze on the letter while maintaining a quiet stance for the duration of a task.

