### Experimental Tasks

The experimental tasks have been designed to simulate eye movements in visually complex environments. Tasks will increase in the level of complexity, starting from easy visual tasks progressing to more visually complex tasks. Letters will be projected in a random sequence on to a range of visually complex background images (Figure 4). The font of the letters, backgrounds, and duration of each task were finalized after piloting. There are 6 tasks, each lasting 70 seconds. The letters appear on the screen for 7 seconds each, at different positions on the screen. Python programming language has been used to select letters and their positions on screen. Participants will be instructed to focus on a letter as they appear on the screen. The tasks increase in difficulty in two ways: (1) the background behind the letter progresses from neutral to busy (ie, to a complex moving background), and (2) by the appearance of either a single letter or multiple letters on screen. In the single-letter tasks (tasks 1, 2, 5, and 6), the participants will be instructed to focus their gaze on each projected letter for the duration of the task. In the multiple letters’ tasks (tasks 3 and 4), the participant will be instructed to find letter *E* and maintain visual fixation on it for the duration of the task. The tasks will be presented from the lowest to highest difficulty of background and number of letters (as described in Figure 4). The tasks will not be randomized as the more difficult tasks might provoke symptoms of dizziness which would hinder the performance of participants in the subsequent tasks.

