### Statistical Analysis

#### Sample Size Calculation

There is a lack of experimental evidence in the population of interest to conduct a power calculation for the required sample size. It is unclear if factors such as age or gender affect visual fixations and there is minimal information on population variation. Therefore, an arbitrary sample size of 20 in each group has been selected. This has been selected in accordance with studies performed in adults with motion sensitivity [33,34]. The data from this study may help inform future studies for the required sample size.

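### COP is down-sampled to 100 Hz before the 5-Hz low-pass filter; unless an anti-alias step is built in, folded noise can inflate mean COP velocity and any cutoff derived from it

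*Protocol article*

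**What the plan says.** In the protocol article, AMTI Force Plates has the platform record forces "at the sampling frequency of 1200 Hz". Postural Sway: Center of Pressure then gives the processing in sequence: the COP series "will be down sampled to 100 Hz and subsequently will be processed using a low-pass filter at 5 Hz", with the filter described as "fourth-order, zero-phase-lag, Butterworth". The outcomes follow: "The mean velocity, root mean square, and maximum range of the COP displacement will be computed". No other filter on the COP signal is named. The article does not say whether the down-sampling includes filtering or averaging, and it gives no noise level or spectrum for the plate.

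The Analysis section compares the groups by one-way ANOVA. It also derives ROC thresholds for gaze, COP and COM parameters, with the cutoff chosen by the Youden index.

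**The concern.** A low-pass filter removes high-frequency noise only while that noise is still at high frequency. Going from 1200 to 100 Hz lowers the Nyquist limit from 600 to 50 Hz. If this is done by keeping one sample in twelve, content above 50 Hz reappears at a lower frequency. Whatever lands below 5 Hz then looks like sway, and the later 5-Hz filter passes it.

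Mean velocity is the exposed outcome. It sums the absolute movement from sample to sample, so in-band noise can only add to it. At stake are the absolute velocities reported and any threshold in mm/s. Such a threshold would carry the noise of this processing order and would not transfer to a laboratory that filters first.

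**Working it through.** There is no figure in the plan to reproduce, so the check is of the processing order itself.

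**Inputs from the article:** 1200 Hz sampling, 100 Hz after down-sampling (factor 12), 5-Hz zero-lag Butterworth, 70 s per task.

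**Assumptions not in the article:** white COP noise of SD σ (0.1 to 1.0 mm at 1200 Hz), equal and independent on both axes; path velocity of 8 or 16 mm/s; plain one-in-twelve decimation; the filter taken as a second-order Butterworth run forward and backward.

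**1. What folds where.** A component at f appears at |f − 100 × round(f/100)|.
- 60 Hz goes to 40 Hz, and 150 and 250 Hz go to 50 Hz. The later filter removes all of these.
- 97 and 103 Hz go to 3 Hz, which stays.
- Exactly 100 Hz goes to 0 Hz and adds no velocity.

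So only bands within about 5 Hz of multiples of 100 Hz matter (95-105, 195-205 Hz and so on). In a one-axis simulation at 8 mm/s, 0.3-mm tones at 50, 60, 100, 150 and 250 Hz left mean velocity within about 0.6% of clean. Tones at 97, 102 and 103 Hz raised it by about 3-7%.

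**2. Noise variance in the 0-5 Hz band.** Decimate first: 5/50 = 10%. Filter first: 5/600 = 0.83%. Ratio: 12.

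**3. Effect on path velocity.** After decimation the noise has spectral density σ²/50 per Hz. Its velocity variance on each axis after the filter is

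4π² × 5³ × (π√2/16) × σ²/50 = 39.48 × 125 × 0.2777 × σ²/50 = 27.4 σ².

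Filtering first divides this by 12, giving 2.28 σ². For two equal Gaussian axes with velocity SD s, the path velocity is s√(π/2) = 1.253 s. Hence s² = (8/1.253)² = 40.7 at 8 mm/s and (16/1.253)² = 163 at 16 mm/s. Inflation = √(1 + 27.4σ²/s²) − 1.

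| σ (mm) | 8 mm/s, as written | 8 mm/s, filter first | 16 mm/s, as written |
|---|---|---|---|
| 0.1 | 0.3% | 0.03% | 0.1% |
| 0.3 | 3.0% | 0.3% | 0.8% |
| 0.5 | 8.1% | 0.7% | 2.1% |
| 1.0 | 29% | 2.8% | 8.1% |

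Two-axis simulations of 70 s agree. As written, they give about 0.5%, 3.0%, 8.8% and 31% at 8 mm/s. Filtered first, they give 0.3%, 0.9% and 2.9% at 0.3, 0.5 and 1.0 mm. At 15.7 mm/s, as written, they give 0.8%, 2.2% and 8.4% for those three noise levels.

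The article splits COP into mediolateral and anterior-posterior components, so velocity may be taken per axis. Simulated on one axis, against anti-aliased down-sampling, the inflation at 8 mm/s is 1.2%, 3.4% and 12% at 0.3, 0.5 and 1.0 mm. At 5 mm/s it is 3.0%, 8% and 29%. The last row matches the two-axis result because 5 × π/2 = 7.9 mm/s of path.

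**4. Effect on the group comparison.** A common floor c turns velocity v into about √(v² + c²). At 1.0 mm, c = √27.4 × 1.253 = 6.6 mm/s. True values of 8.2 and 12.2 mm/s become √(67.2 + 43.6) = 10.5 and √(148.8 + 43.6) = 13.9, so the ratio drops from 1.49 to 1.32.

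The spread between people shrinks as well. With assumed log-normal variation between people (CV 24% or 37%), Cohen's d goes from 1.58 to 1.54 or from 1.05 to 1.02, a fall of about 3%. The AUC goes from 0.880 to 0.878 or stays at 0.786. At 0.5 mm, d falls about 1%.

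**5. Other COP outcomes.** In simulation, RMS changes by 0.3% or less and range by about 1%.

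**The case against.** The strongest reply is that the article says only that the series is down-sampled. It does not say that samples are discarded unfiltered. Down-sampling routines can include an anti-alias filter or averaging, the acquisition hardware may filter too, and a condensed article may leave such detail to the full protocol. This stands, and it makes the finding conditional. It does not remove the finding, because the article fixes the order of its two named steps and the better order costs nothing.

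The noise level is also assumed. At 0.1 mm or below the inflation is about 0.5% or less, and real plate noise need not be white. This stands too, which is why a range is given and no single figure.

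A reader might infer three stronger things that the documents do not support:
- *All noise above 50 Hz contaminates the sway band.* It does not; only the narrow bands around multiples of 100 Hz survive the later filter.
- *The group contrast is materially weakened.* The ratio and raw difference can shrink, but the plan analyses neither a ratio nor an unstandardised threshold difference. ANOVA depends on the difference relative to the spread, and the ROC curve on ranking. Both are nearly unchanged when the noise floor is common.
- *The bias differs between groups through body weight.* The article gives no weights and no reason to expect a difference.

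**Conclusion.** The point holds in a limited, conditional form. As written, the only named COP filter comes after decimation and cannot remove noise already folded below 5 Hz. If no anti-alias step precedes it, mean COP velocity is biased upward. Under the assumed white noise, the bias at a path velocity of 8 mm/s runs from about 0.5% (0.1 mm) to about 30% (1.0 mm). At 16 mm/s it runs from about 0.2% to 9%.

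The exposure is the absolute velocity and a Youden cutoff expressed in mm/s. The standardised group difference, AUC, RMS and range are little affected, provided the noise floor is similar across participants. No stated design quantity depends on this, since "an arbitrary sample size of 20 in each group has been selected". It is a minor, free improvement. It does not show that the sway comparison is invalid.

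**What to change.** Reverse the two steps: apply the fourth-order, zero-lag 5-Hz Butterworth filter to the 1200-Hz COP series, then down-sample to 100 Hz, and say so in the section on postural sway. If the down-sampling routine already applies an anti-alias filter below 50 Hz, one sentence stating this is enough.

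The cost is one line of processing code and a re-run on the raw files, assuming these are kept at 1200 Hz. The Results section says the data were still being processed and that analysis would start in July 2020, so the change precedes the analysis. It has no statistical downside.

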#### Kinematics

Raw data from the Qualisys motion analysis will be imported into Visual 3D, where a 6 degree-of-freedom model will be constructed. Data will be interpolated and processed using a fourth-order Butterworth low-pass filter with cutoff frequency of 12 Hz. The body COM and the COM of the head segment will be calculated using a pipeline in Visual 3D. The mean velocity, root mean square, and maximum range of the COM of the head and whole-body displacement will be calculated [47].

### Safety Measures

The study will be using moving background/moving images, which may induce dizziness, imbalance, or nausea in some participants. An assistant will stand close to the participant to provide assistance and prevent a fall in case of imbalance. We will monitor how a participant is feeling throughout each task, and appropriate rest intervals will be provided. The session would be stopped at any stage if required.

In the unlikely event of a physical injury, rehabilitation and compensation for injury by accident may be available from the Accident Compensation Corporation, provided the incident details satisfy the requirements of the law and the Corporation’s regulations.

### Statistical Analysis

#### Sample Size Calculation

There is a lack of experimental evidence in the population of interest to conduct a power calculation for the required sample size. It is unclear if factors such as age or gender affect visual fixations and there is minimal information on population variation. Therefore, an arbitrary sample size of 20 in each group has been selected. This has been selected in accordance with studies performed in adults with motion sensitivity [33,34]. The data from this study may help inform future studies for the required sample size.

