### Trial Design, Setting, and Participants

This is a cross-sectional exploratory single-session experimental study that will be laboratory based in Auckland University of Technology. A total of 40 adults will participate in the study (20 healthy adults and 20 adults with motion sensitivity after vestibular disorder). Healthy adults aged between 18 and 60 who are independently mobile and have no history of neurological conditions will be recruited through neurorehabilitation research team networks and community advertisements. Adults with motion sensitivity will be recruited through a specialized vestibular disorders clinic. They will be included if they have had a history of vestibular disorder (confirmed by a clinician in the vestibular disorder clinic) but have no current signs of acute vestibular deficits, are aged between 18 and 60 [40,41], have a history of motion sensitivity symptoms as reported by the Visual Vertigo Analogue Scale (score >5) [42-44], and score >40 on the Dizziness Handicap Inventory [44]. People with a history of previous eye surgery, or a medical condition that may influence eye movements such as sarcoidosis, Lyme disease, diabetes mellitus, traumatic brain injury, and migraine will be excluded from the study.

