#### Analysis

Descriptive statistics (mean and standard deviation) will be calculated for each of the variables. Data normality will be examined using the Kolmogorov–Smirnov statistic. One-way independent-measures analyses of variance will be performed to investigate the differences between groups for all variables. Post-hoc analysis with Šidák adjustment will be used for multiple comparisons [48]. Finally, a receiver operating characteristic curve analysis will be applied to determine threshold values in gaze, COP, and COM parameters, allowing identification of the impairment induced by motion sensitivity. The optimal cutoff point will be determined using the Youden Index. Areas under the curve, specificity, and sensitivity will also be calculated. Values of areas under the curve will be categorized as follows: excellent (≥0.90), good (0.80-0.90), fair (0.70-0.79), and poor (<0.70).

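### Unmatched groups from different sources are compared with group as the only factor, so an age or sex imbalance would enter the group contrasts and the ROC cutoffs

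*Protocol article*

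**What the plan says.** The section Trial Design, Setting, and Participants sets up two existing groups without random allocation: "20 healthy adults and 20 adults with motion sensitivity after vestibular disorder". Healthy adults "will be recruited through neurorehabilitation research team networks and community advertisements". For the other group: "Adults with motion sensitivity will be recruited through a specialized vestibular disorders clinic". The age limits are the same in both groups, 18 to 60. No matching, stratification or frequency balancing on age or sex is described.

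The Sample Size Calculation section, in explaining why no power calculation was possible, says: "It is unclear if factors such as age or gender affect visual fixations and there is minimal information on population variation".

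The Analysis section then names the model: "One-way independent-measures analyses of variance will be performed to investigate the differences between groups for all variables". It goes on to ROC curves with Youden cutoffs for the gaze, COP and COM parameters, with the stated purpose of "allowing identification of the impairment induced by motion sensitivity".

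**The concern.** A one-way ANOVA on group has no term for age or sex. In a randomised comparison that would be unbiased. Here the groups are defined by disease status and reach the study by different routes, so their age and sex composition can differ systematically as well as by chance. If age or sex is related to an outcome, part of the group difference is then an age or sex difference, and the planned model cannot separate the two.

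The same unadjusted contrast feeds the AUCs and cutoffs, so a threshold could partly separate older from younger people, or women from men, and still be reported as a marker of motion sensitivity. The Discussion intends the results to inform diagnostic and rehabilitation programmes and, if characteristics are altered, to lead to an intervention.

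**Working it through.** The plan gives no figure to reproduce: the sample size is described as arbitrary, with no effect size, SD or power. The check is therefore how an unadjusted comparison of 20 versus 20 behaves when ages differ.

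**Inputs from the article.** 20 per group; ages 18 to 60 in both; group as the only factor.

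**Assumed inputs (not in the article).**
- Age SD: that of a uniform distribution on 18 to 60, (60 − 18)/√12 = 42/3.464 = 12.1 years.
- Within-group age-outcome correlation r: 0 to 0.4.
- Difference in mean age D: 5 or 10 years.
- No true group effect; two-sided test at 5%.

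**Formulas.** Spurious standardised difference: d = r × D / 12.1. Noncentrality of the two-group t-test (equivalent to the one-way ANOVA): d × √(20/2) = 3.162 d. Rejection rate: noncentral t with 38 df, critical value 2.024.

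**Example.** For D = 10 and r = 0.3, d = 0.3 × 10/12.12 = 0.247. The noncentrality is 0.78 and the rejection rate 11.9%.

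| r | D = 5: d | D = 5: rejection | D = 10: d | D = 10: rejection |
|---|---|---|---|---|
| 0 | 0 | 5.0% | 0 | 5.0% |
| 0.1 | 0.04 | 5.2% | 0.08 | 5.7% |
| 0.2 | 0.08 | 5.7% | 0.16 | 8.0% |
| 0.3 | 0.12 | 6.7% | 0.25 | 11.9% |
| 0.4 | 0.16 | 8.0% | 0.33 | 17.4% |

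**How likely such imbalances are.** If both groups came from the same uniform age distribution, the standard error of the difference in mean age would be 12.12 × √(2/20) = 3.83 years. By the normal approximation, a gap of 5 years or more in either direction would occur in about 19% of samples, and one of 10 years or more in about 1%. Chance alone can readily produce the first. The second would in practice need recruitment routes that draw different ages.

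**Sex.** In a simulation with 50% versus 80% of one sex and an assumed sex effect of 0.5 SD, the unadjusted test rejected in 7.7% of runs and the adjusted test in 5.1%.

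**Does adjustment work, and what does it cost?** The simulation (20,000 runs per scenario) compared the one-way ANOVA (38 error df) with an ANCOVA on group, age and sex (36 error df).
- With no true effect, the ANCOVA rejected in 5.0% to 5.3% of runs in every scenario. The unadjusted test rejected in 11.9% at r = 0.3, D = 10.
- With a true effect of 0.9 SD and balanced ages, power went from 0.79 to 0.77 at r = 0 and from 0.79 to 0.81 at r = 0.3.
- With a true effect of 0.9 SD, D = 10 and r = 0.3, adjusted power was 0.74. The unadjusted 0.94 is not a fair comparison, because there the bias adds to the effect.

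**The case against.** A reader might infer that the authors concede that age and gender affect the outcomes and then ignore it. The text does not support that. It says only that an effect is unclear, refers to visual fixations and not to COP or COM, and appears as a reason for having no power calculation. It leaves the question open and asserts nothing.

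A reader might also take a false-positive rate of 12% to 17% as the expected harm. That range needs a 10-year imbalance together with a correlation of 0.3 to 0.4, and neither figure is in the article. At r = 0 there is no harm at all.

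Three further points deserve weight:
- The shared age limits, and the exclusion of eye surgery and of conditions that may influence eye movements, are real control by restriction. They bound an imbalance but do not balance ages within a 42-year range.
- A journal article commonly leaves demographic tables, recruitment balancing and sensitivity analyses to fuller documents, so their absence is no finding. This does not rescue the Analysis section, which is not silent: it names a group-only model for all variables.
- The study calls itself exploratory. That explains the small sample, but not a reading of ROC cutoffs as impairment caused by the condition.

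**Conclusion.** The point holds in a limited form. The article commits to an unadjusted comparison of two non-randomised, differently recruited groups while leaving open whether age or gender influences visual fixations. For COP and COM it says nothing either way. An imbalance would be carried into both the group contrasts and the ROC cutoffs.

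The actual bias is unknown: the article gives no group age distribution, no sex distribution and no age-outcome correlation. Under the stated assumptions the false-positive rate runs from the nominal 5% to 8.0% for a 5-year gap and to 17.4% for a 10-year gap. These figures show sensitivity to the assumptions and do not predict this study's error rate. The finding does not say that 20 per group is wrong. The change should be made, because it is cheap and protects the main interpretation.

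**What to change.** In the Analysis section, replace the one-way ANOVA by a group comparison with age (continuous) and, where it was recorded, sex as covariates (ANCOVA) for each variable. Report the unadjusted contrast beside it. Age should be available, since it is an eligibility criterion; the article does not state that sex is recorded.

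For the ROC analysis, either give a covariate-adjusted AUC and cutoff, or reword the stated purpose so that it claims association with motion sensitivity and not causation by it.

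The Results section reports that data collection is complete and analysis has not begun, so matching is no longer possible but this change is. It costs analysis wording, about two error degrees of freedom, and some precision if the groups differ strongly in age (adjusted power of about 0.74 at a 0.9 SD effect in the 10-year, r = 0.3 illustration).

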#### Analysis

Descriptive statistics (mean and standard deviation) will be calculated for each of the variables. Data normality will be examined using the Kolmogorov–Smirnov statistic. One-way independent-measures analyses of variance will be performed to investigate the differences between groups for all variables. Post-hoc analysis with Šidák adjustment will be used for multiple comparisons [48]. Finally, a receiver operating characteristic curve analysis will be applied to determine threshold values in gaze, COP, and COM parameters, allowing identification of the impairment induced by motion sensitivity. The optimal cutoff point will be determined using the Youden Index. Areas under the curve, specificity, and sensitivity will also be calculated. Values of areas under the curve will be categorized as follows: excellent (≥0.90), good (0.80-0.90), fair (0.70-0.79), and poor (<0.70).

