**Objective:**

The main aim of this exploratory observational study is to investigate visual fixations and postural sway in response to increasingly complex visual environments in healthy adults and adults with motion sensitivity.

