## Methods

### Aim

To conduct an observational study with 40 adults (20 in each group; healthy adults and adults with motion sensitivity). The study will determine whether complex visual environments are associated with fixational instability, altered COP displacement, and altered center of mass (COM) displacements of the head and body in adults with motion sensitivity compared with healthy adults.

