### Hypothesis

Complex visual environments in people with motion sensitivity compared with healthy adults will be associated with (1) increased number of visual refixations, (2) increased displacement of COP, and (3) differences in the body COM displacement and differences in the head COM displacement.

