## Discussion

This is an exploratory study with the primary aim to identify whether fixational instability is associated with motion sensitivity and whether it leads to increased postural sway and altered kinematics in adults with motion sensitivity.

This study will provide a detailed investigation of visual fixations, postural sway, and kinematics in complex visual environments. The use of a mobile eye tracker device will investigate naturalistic eye behavior when exposed to experimental stimuli. The task hierarchy will help in understanding how characteristics of visual fixations change when a person views a complex visual environment as opposed to neutral environments. The experimental tasks might provoke symptoms in some participants; however, we expect that all participants will be able to complete the protocol with appropriate rest intervals between tasks. Our sample size of 20 participants in each group is a foundational step in exploring whether visual fixations contribute to motion sensitivity after vestibular disorder. We anticipate the outcomes will be able to detect a difference between healthy adults and those with motion sensitivity. Results from this study will inform future trials and will be used to inform development of diagnostic and rehabilitation programs.

We hope that this study will increase our understanding of the complex interactions of vision and balance in people with motion sensitivity. If we determine that gaze and postural control characteristics are altered, we will develop an intervention that is designed to re-align the gaze and postural control characteristics closer to those of the control population. This intervention would then be tested in a series of clinical trials to determine effectiveness.

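### The planned ANOVA compares groups only and has no task term, so it cannot show that a patient–control difference is specific to complex visual environments

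*Protocol article*

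**What the plan says.** **The question.** The Objective in the Abstract is to "investigate visual fixations and postural sway in response to increasingly complex visual environments in healthy adults and adults with motion sensitivity". The Aim reads "The study will determine whether complex visual environments are associated with fixational instability", with further outcomes, in adults with motion sensitivity relative to healthy adults. The Hypothesis begins "Complex visual environments in people with motion sensitivity compared with healthy adults will be associated with (1) increased number of visual refixations" and goes on to centre-of-pressure and centre-of-mass displacement. The Discussion presents the graded tasks as a way to learn "how characteristics of visual fixations change when a person views a complex visual environment as opposed to neutral environments".

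**The design.** Under Experimental Tasks, there are six tasks of 70 seconds each, all done in one session. Backgrounds go from neutral to busy and moving. Tasks 1, 2, 5 and 6 show a single letter, and tasks 3 and 4 show several. Order is fixed: "The tasks will be presented from the lowest to highest difficulty of background and number of letters".

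**The test.** The Analysis section gives one inferential comparison: "One-way independent-measures analyses of variance will be performed to investigate the differences between groups for all variables". It adds "Post-hoc analysis with Šidák adjustment will be used for multiple comparisons", without saying which comparisons are meant. The ROC analysis that follows also only separates the two groups. No task factor, repeated-measures structure or group-by-task term is named anywhere in the article.

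**The concern.** A one-way ANOVA on two groups asks a single question: do the group means differ? Applied to a complex task, it answers that for the complex task alone. The neutral background is there to serve as a reference, but the named test never uses it.

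This matters because a group difference on every background is plausible. Patients enter on the strength of their symptom and handicap scores (Trial Design, Setting, and Participants), and the Introduction treats unstable fixation as something that may predispose a person to motion sensitivity. If patients refixate or sway more on every background, the test will tend to be significant in the complex tasks too. Nothing in it would tell that apart from a response to complexity. The Discussion intends to build an intervention on altered gaze and postural control, so the distinction has consequences.

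**Working it through.** The plan gives no alpha, SD, effect size or between-task correlation, and it calls 20 per group arbitrary. There is therefore no figure of its own to reproduce.

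**Inputs.** From the protocol: 20 per group, six tasks per person, group as the only factor. Assumed: two-sided alpha 0.05; equal SD in every task; the same correlation ρ between any two tasks of one person (0.3, 0.5 or 0.7); and, for the rising case, a linear rise over tasks 1 to 6. The linear rise is a simplification, because the tasks vary in both background and letter number.

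**Step 1: what each test targets.** Let δₖ be the patient–control difference at task k, in SD units.
- The one-way test at task 6 tests δ₆ = 0.
- A claim specific to complexity needs δ₆ − δ₁ ≠ 0, or a slope of δₖ over tasks.

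Constant offset: δ₆ = 0.8 and δ₆ − δ₁ = 0.8 − 0.8 = 0. Rising offset: δ₆ = 0.8 and δ₆ − δ₁ = 0.8 − 0 = 0.8. The two cases have the same δ₆, so no test of δ₆ can separate them.

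**Step 2: one-way test at task 6.** With two groups it equals a t test with 38 df and noncentrality d√(n/2) = 0.8 × √10 = 2.53. Exact power is 0.693. Simulation (20,000 trials per scenario) gives 69–70% for both the constant and the rising offset.

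If the Šidák step covers six tasks, the per-test alpha is 1 − 0.95^(1/6) = 0.0085 and the exact figure is 0.415. Simulation gives 41–42% in both cases, so the adjustment lowers the rate but does not separate them.

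**Step 3: group-by-task test, constant offset.** Tested as the group difference in each person's slope, or in the change from task 1 to task 6, it rejects in 4.7–5.3% of trials. This covers offsets of 0.5, 0.8 and 1.0 SD and all three correlations.

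**Step 4: power under the rising offset.** The within-person change has SD √(2(1 − ρ)), so its noncentrality is 0.8√10 / √(2(1 − ρ)).

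| ρ | SD of change | Noncentrality | Change test, tasks 1 to 6 (simulated) | Slope test, six tasks (simulated) | One-way test, task 6 (simulated) |
|---|---|---|---|---|---|
| 0.3 | √1.4 = 1.18 | 2.14 | 55% | 69% | 69% |
| 0.5 | 1.00 | 2.53 | 69% | 83% | 70% |
| 0.7 | √0.6 = 0.77 | 3.27 | 89% | 96% | 69% |

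The two-task change test equals the one-way test in power at ρ = 0.5, is weaker below that and stronger above it.

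**The case against.** The strongest reply is that the Hypothesis can be read narrowly, as a group difference during complex tasks. A one-way test per task does address that. This stands: a reader might infer that the plan cannot test its hypothesis at all, and the text does not support so absolute a claim. The Discussion sentence on complex versus neutral scenes does not mention groups either, so alone it implies a task effect rather than an interaction. But the named ANOVA has no task effect, and the Objective and Aim put response to complexity and group comparison together. Even on the narrow reading, a difference equally present on the neutral background could not be credited to complex environments.

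The study is exploratory, and planned means and SDs might reveal a constant offset. That limits the harm, but comparing means across tasks by eye is not a test.

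Several stronger readings are tempting and should not be drawn:
- **Inflated type I error from entering six records per person as independent rows.** The text never says this will be done, and it defines the fixation measures per trial, which points to analysis by task.
- **The 69% as a false-positive rate.** It is ordinary power to detect a real group offset.
- **Significance at task 6 but not at task 1 as a bias toward complexity.** Under a constant 0.8 SD offset this pattern appears in 11–18% of simulated trials, but by symmetry its reverse is equally frequent.
- **Loss of data from stopped sessions.** Per-task tests use everyone who did that task, and the Discussion expects all participants to finish.
- **A contradictory task order.** Tasks are ordered jointly on background and letter number by reference to Figure 4, which is not available here.

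**Conclusion.** The point holds in a limited form. The stated test can show a group difference in a complex task, but it cannot show that the difference is specific to complexity. That follows from the model and needs no assumption. The figures only illustrate it: about 69% significance at task 6 under both a constant 0.8 SD offset and one rising from 0 to 0.8 SD, against about 5% rejection by a group-by-task test under the constant offset. They rest on assumed alpha, effect sizes, equal SDs and correlations.

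An unseen analysis plan does not remove the point, because the protocol names this test in both the Abstract and the Methods. The argument for change is validity for the stated question. A gain in power is not assured. Nor would an interaction test isolate complexity completely, since the fixed order ties complexity to time on task.

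**What to change.** Replace the one-way ANOVA with a mixed model for each outcome: linear for continuous measures, and a count model for refixations and saccades. Include group, background complexity, single or multiple letters, group-by-background and group-by-letter terms, and a participant random effect.

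Name the group-by-background contrast as the test of the complexity hypothesis. Define it from the task definitions in Figure 4, comparing tasks with the same letter condition where possible. For count outcomes, state the scale on which the contrast is made.

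Report the group difference in each task as an estimate with a confidence interval, which also serves the narrow reading of the Hypothesis. State that, because tasks run in a fixed order, the contrast reflects complexity plus time on task.

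The cost is a change of analysis wording and slightly more modelling. The design already collects the required data, and the Results section says that analysis had not yet begun.
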